## Abstract

**Introduction:**

Age-related health, brain, and cognitive impairment is a great challenge in current society. Cognitive training, aerobic exercise and their combination have been shown to benefit health, brain, cognition and psychological status in healthy older adults. Inconsistent results across studies may be related to several variables. We need to better identify cognitive changes, individual variables that may predict the effect of these interventions, and changes in structural and functional brain outcomes as well as physiological molecular correlates that may be mediating these effects. Projecte Moviment is a multi-domain randomized trial examining the effect of these interventions applied 5 days per week for 3 months compared to a passive control group. The aim of this paper is to describe the sample, procedures and planned analyses.

**Methods:**

One hundred and forty healthy physically inactive older adults will be randomly assigned to computerized cognitive training (CCT), aerobic exercise (AE), combined training (COMB), or a control group. The intervention consists of a 3 month home-based program 5 days per week in sessions of 45 min. Data from cognitive, physical, and psychological tests, cardiovascular risk factors, structural and functional brain scans, and blood samples will be obtained before and after the intervention.

**Results:**

Effects of the interventions on cognitive outcomes will be described in intention-to-treat and per protocol analyses. We will also analyze potential genetic, demographic, brain, and physiological molecular correlates that may predict the effects of intervention, as well as the association between cognitive effects and changes in these variables using the per protocol sample.

**Discussion:**

Projecte Moviment is a multi-domain intervention trial based on prior evidence that aims to understand the effects of CCT, AE, and COMB on cognitive and psychological outcomes compared to a passive control group, and to determine related biological correlates and predictors of the intervention effects.

**Clinical Trial Registration:**
www.ClinicalTrials.gov, identifier NCT03123900.

## Introduction

*Walk, learn, be active, do!* A large number of messages about healthy behaviors to reduce age-related functional decline has flooded into our daily lives. Aging is related to major risk of cardiovascular diseases, metabolic syndrome, mitochondrial dysfunction, obesity, sarcopenia, and consequent higher inflammation, oxidative stress, and brain and cognitive impairment (Sallam and Laher, 2016). Healthy aging has become a matter of interest for the scientific community and for most people and governments that stand for social health policies. Since the aged population is expected to triple by 2100 and will represent 29% of people in the world (United Nations Department of Economic Social Affairs Population Division, 2017), we need policies and strategies that enhance independence and quality of life while considering economic, social, environmental, and personal determinants as well as health and social services (World Health Organization [WHO], 2002, 2015). Cognitive training and aerobic exercise are two lifestyle interventions that have proved to produce positive effects on health (Cotman et al., 2007; Sallam and Laher, 2016), reduce cognitive impairment (Harada et al., 2013), and delay the onset of dementia (Hall et al., 2009). However, questions about which, when and why remain unclear.

Gates and Valenzuela (2010) define cognitive training as an intervention consisting of repeated practice of standardized exercises targeting a specific cognitive domain or domains. Computerized cognitive training (CCT) has emerged as a new tool to systematically apply these exercises. CCT facilitates the administration by allowing investigators to adapt the content and challenge of the task to individual performance and including visual engaging interfaces (Lampit et al., 2014; Shao et al., 2015). There is evidence that CCT may maintain or improve global cognitive function and specific trained functions such as verbal memory (Shao et al., 2015; Barban et al., 2016; Bahar-Fuchs et al., 2017), processing speed (Kueider et al., 2012; Lampit et al., 2014; Shao et al., 2015), and executive function (Kueider et al., 2012; Barban et al., 2016). Brain related benefits such as increases in gray matter volume of default-mode network (DMN) areas (De Marco et al., 2016), functional activity of frontal-parietal networks (Klingberg, 2010; Jolles et al., 2013; Kim et al., 2017) and connectivity of the hippocampus (Lisanne et al., 2017) and posterior DMN (De Marco et al., 2016) have also been described. These structural and functional changes appear to be directly related to the types of trained tasks (Taya et al., 2015). Despite this, the biological pathways by which CCT produces these effects remain poorly understood in humans. Shao et al. (2015) hypothesized that these mechanisms might be related to brain neuroplasticity. According to Hebb (1949), a group of neurons that are repeatedly and simultaneously activated will tend to form stronger associations. This framework suggests that CCT may influence cognition by promoting the strength of synaptic connections (Patterson et al., 1996; Taya et al., 2015). Based on animal models, Valenzuela and Sachdev (2009) suggested that brain-derived neurotrophic factor (BDNF) and nerve growth factor (NGF) might be the molecules promoting cell survival and proliferation after cognitive stimulation in humans.

Physical activity (PA), defined as any body movement produced by skeletal muscles that results in energy expenditure (Caspersen et al., 1985), promotes health, cognitive and psychological benefits (DiLorenzo et al., 1999; Penedo and Dahn, 2005). Exercise, which is considered a planned, structured and repetitive subtype of PA that aims to improve physical fitness (Caspersen et al., 1985), produces an acute body reaction that includes increased energy expenditure, repetitive muscle contractions and an inflammatory and oxidative response (van Praag et al., 2014; Sallam and Laher, 2016). Different types of exercise, applied in a regular manner, may produce different physiological, brain and cognitive benefits (Barha et al., 2017; Cabral et al., 2019). Several systematic reviews conclude that aerobic exercise (AE), the type of exercise that involves oxygen consumption and movement of large groups of skeletal muscles during a sustained period of time (Chodzko-Zajko et al., 2009; Thomas et al., 2012), may improve executive function, processing speed, attention and memory in healthy older adults (Etnier et al., 1997; Colcombe and Kramer, 2003; Paterson and Warburton, 2010; Smith et al., 2010; Guiney and Machado, 2012; Karr et al., 2014; Scherder et al., 2014; Lü et al., 2016; Barha et al., 2017; Northey et al., 2017). However, other reviews reported that the evidence was too limited to draw firm conclusions (Snowden et al., 2011; Cox et al., 2016; Brasure et al., 2017; Sáez de Asteasu et al., 2017) or reported no significant effects of exercise on cognition (Angevaren et al., 2007; Kelly et al., 2014; Young et al., 2015). Regular AE has direct effects on our body: higher oxygen and glucose consumption related to increased energy expenditure, and reduction of body fat and increased muscle strength, which have been hypothesized as specific pathways for the physiological relationship between exercise and cognitive function (Cotman et al., 2007; van Praag et al., 2014; Sallam and Laher, 2016; Stimpson et al., 2018). The increase of energy expenditure reduces visceral fat that may lead to less production of interleukin-6 (IL-6), tumor necrosis factor alpha (TNF-alpha) and an increase of M2:M1 macrophage ratio and the release of adiponectin. Energy expenditure is also related to higher glucose consumption which may be related to better energy metabolism and insulin sensitivity and reducing resistance to leptin and insulin (van Praag et al., 2014). The activity in the muscles induces IL-ra, IL-10, and heat shock proteins (HSP), reducing the inflammatory environment while suppressing IL-1 and TNF-alpha and upregulating IL-15 and promoting the reparation of the vessels to facilitate blood flow and, as a consequence, oxygen and nutrient circulation (Sallam and Laher, 2016). Skeletal muscles may also improve the use of lipids instead of glycogen in energy expenditure processes. Exercise increases circulating HDL and reverses cholesterol transport, reducing cholesterol levels in blood (Mann et al., 2013). The activity in the cardiovascular system produces laminar shear stress on vascular endothelial cells which may be related to the downregulation of oxidative processes, and activates the hypothalamic-pituitary-adrenal axis which triggers the release of glucocorticoids that may help to inhibit the inflammatory system. The anti-oxidative response is mediated by redox-sensitive transcription factors: NF-KB and AP-1, which reduce RONS, and PGC-1, which promotes mitochondrial biogenesis (Sallam and Laher, 2016). Laminar shear stress is also related to greater release of insulin growth factor (IGF) and vascular endothelial factor (VEGF) which benefits the cardiovascular system, helping to repair the body vasculature and promoting greater blood flow, brain angiogenesis and neurogenesis (Cotman et al., 2007; Sallam and Laher, 2016; Stimpson et al., 2018; Cabral et al., 2019). IGF promotes the release of BDNF in the brain, which has been identified as one of the principal factors mediating the effect of exercise on cognition. BDNF may support newborn cells, regulate synaptic changes and facilitate long-term potentiation which may be related to the identified brain changes and cognitive benefits (Stimpson et al., 2018; Cabral et al., 2019). Cardiorespiratory fitness (CRF), the health-related component of physical fitness reflecting these parameters, has shown to be related to better cognitive function in healthy adults (Colcombe and Kramer, 2003). However, Etnier et al. (2006) and Young et al. (2015) could not find the relationship between changes in CRF and changes in cognition in their systematic reviews. Erickson et al. (2014) found a positive relationship between PA or CRF and gray matter volume in older adults in prefrontal, temporal and parietal areas (Erickson et al., 2007; Gordon et al., 2008; Weinstein et al., 2012). Higher levels of CRF have been also related to greater hippocampus volume and memory performance (Erickson et al., 2009; Szabo et al., 2011) and bigger caudate nucleus and nucleus accumbens (Verstynen et al., 2012). However, Rosano et al. (2010) and Smith et al. (2011) did not find a significant association between PA and gray matter volume. Sexton et al. (2016) systematically reviewed the effects of exercise on white matter volume – global, local, lesions, and microstructure – and found cautious support for this association given the fact that evidence was inconsistent. Recent research aims to identify the effect of exercise on functional connectivity. CRF has been associated with higher general efficiency and lower local efficiency and executive function performance (Kawagoe et al., 2017). Brain network modularity at baseline may predict the effects of exercise intervention (Baniqued et al., 2018). Other variables have been identified as potential modifiers of the association between exercise and cognition. Groups with a higher percentage of women (Barha and Liu-Ambrose, 2018) or APOE E4 genotype carriers (Etnier et al., 2007) may benefit more from exercise.

The combination (COMB) of PA and cognitive stimulation may induce greater cognitive benefits compared to each intervention separately (Kraft, 2012; Curlik and Shors, 2013; Fissler et al., 2013; Bamidis et al., 2014; Law et al., 2014; Lauenroth et al., 2016). However, Shatil (2013) found improvements only on those participants engaged in cognitive training, single or combined. Zhu et al. (2016) replicated these results in a systematic review of twenty studies, concluding that COMB may have a small positive effect only when compared to a control and physical activity group but not to a cognitive intervention. To our knowledge, the specific cognitive benefits of COMB, in sequence or dual task, remain unknown; undefined “greater effects” or “more enduring” are usually hypothesized. General cognitive function (Oswald et al., 2006; Shatil, 2013), executive function (Anderson-Hanley et al., 2012; Theill et al., 2013; Barcelos et al., 2015; Eggenberger et al., 2015), processing speed (León et al., 2015), memory (Fabre et al., 2002) and vocabulary (Schmidt-Kassow et al., 2013) performance may tend to benefit more from a COMB. However, evidence is not consistent across trials and negative results have also been found in these same domains (Fabre et al., 2002; Oswald et al., 2006; Legault et al., 2011; Anderson-Hanley et al., 2012; Linde and Alfermann, 2014; Rahe et al., 2015). Li et al. (2014) and Pieramico et al. (2012) reported that a multimodal intervention produced a reorganization of functional connectivity between the DMN areas. Shah et al. (2014) identified higher verbal memory related to increased glucose metabolism in the brain in the COMB group only. In order to explain these potential greater benefits, Olson et al. (2006) and Fabel et al. (2009), based on animal models, hypothesized that neuroplasticity may be facilitated by exercise and guided by cognitive training. The anti-inflammatory, anti-oxidative stress and cardiovascular and neural repairing responses related to regular PA may enhance cell proliferation through BDNF. Cognitive stimulation may promote the survival of newborn cells and regulate synaptic changes (Hebb, 1949).

Systematic reviews and papers cited before, independently of the intervention, reported inconsistencies across results which likely relate to genetic and environmental variables of participants; type, duration and schedule of assessments; type, duration, frequency, intensity and adherence of interventions; as well as methodological issues of the design, such as type of control group and statistical approaches (Kraft, 2012; Young et al., 2015; Gates et al., 2019). These discrepancies challenge a clear theoretical model and lead to different conclusions and the identification of potential moderators even at the systematic and meta-analytic analysis level. These issues highlight the need to better identify not only the cognitive effects of these interventions but also the individual variables that may predict them and the brain changes and physiological molecular correlates that may be mediating any benefits.

Projecte Moviment is a multi-domain randomized trial that addresses the effect of CCT, AE, and COMB on cognition and psychological status in healthy physically inactive older adults compared to a passive control group. We also aim to identify variables that may predict the effects of the intervention and the underlying brain changes and physiological molecular correlates that may mediate the effects. The purpose of this paper is to describe the protocol in accordance with SPIRIT Guidelines.

## Aims of the Study

The primary objective of Projecte Moviment is to examine the effect of CCT, AE, or COMB on cognitive outcomes in healthy physically inactive older adults. The primary hypotheses sustaining this goal are:

1.Computerized cognitive training – 5 times per week for 3 months – will improve general cognitive function as well as trained cognitive functions (executive function, processing speed and memory) measured by composite scores using a battery of validated neuropsychological tests at 3 months compared to a control group.2.Aerobic exercise – 5 times per week for 3 months – will improve executive function, attention-processing speed and memory measured by composite scores using a battery of validated neuropsychological tests at 3 months compared to a control group.3.Combined training – 5 times per week for 3 months – will show greater improvements in general cognitive function, executive function, attention-processing speed and memory measured by composite scores using a battery of validated neuropsychological tests at 3 months compared to a control group.

The secondary objectives of Projecte Moviment are: (a) to determine the effects of these interventions on psychological status and subjective performance on daily activities, CRF, brain structure and function and physiological molecular correlates; (b) to identify genetic, demographic, physiological and brain variables that might predict the effect of the intervention; (c) to identify the association between cognitive effects and other psychological, physiological correlates. Specific hypotheses for each objective will be specified in each article when reporting results. General secondary hypotheses include:

1.All intervention conditions will positively impact psychological and subjective daily functional performance assessed by questionnaires compared to controls.2.Aerobic exercise and COMB will similarly increase CRF and energy expenditure in daily activity compared to cognitive and control conditions.3.All intervention conditions will positively impact the structure and function of the brain assessed by whole brain analyses, structures of interest and white matter lesions volume and microstructure, cortical thickness and functional connectivity compared to a control group.4.Aerobic exercise and COMB will improve immunity, reduce inflammation and improve vascular risk factors compared to cognitive and control conditions.5.Individual variables (i.e., sex, age, cognitive baseline, CRF baseline) will predict the effect of the interventions on cognition.6.Changes in cognition will be related to specific changes in secondary outcomes depending on the intervention.

## Methods

### Study Oversight and Schedule

Projecte Moviment is a multi-center, single-blind randomized controlled trial that started November 2015 with the aim of recruiting 140 participants distributed in four parallel groups (one control group, *n* = 20; three intervention groups, *n* = 40 each). All participants give their written informed consent and are assessed at baseline and 3 months later, immediately after the intervention (Figure 1). This study is led by the Faculty of Psychology of the University of Barcelona in collaboration with Institut Universitari d’Investigació en Atenció Primària Jordi Gol, Hospital Germans Trias i Pujol and Institute Guttmann; it was approved by the responsible ethics committees following the Declaration of Helsinki.

**FIGURE 1 F1:**
[figure not shown]
Projecte Moviment study design. CCT, computer-based cognitive training; AE, aerobic exercise; COMB, combined training.

### Participants

Participants are 140 community dwelling physically inactive healthy adults aged 50–70 years from Barcelona. Inclusion and exclusion criteria are detailed in Table 1. Multiple strategies are applied to recruit participants: distribution of posters and flyers, publication of press releases in local media (newspapers, radio, and TV), presentations in local community organizations, list of patients of general physicians and volunteers from previous studies. Participants are enrolled in primary care centers and can voluntarily withdraw from the project at any time.

**TABLE 1 T1:** Inclusion and exclusion criteria for Projecte Moviment.

**Inclusion criteria**	**Exclusion criteria**
Aged 50–70 years	Current participation in any cognitive training activity or during last 6 months > 2 h/week
≤120 min/week of physical activity during last 6 months	Diagnostic of dementia or mild cognitive impairment
Mini-Mental State Examination (MMSE) ≥ 24	Diagnostic of neurological disorder: stroke, epilepsy, multiple sclerosis, traumatic brain injury, brain tumor
Montreal Cognitive Assessment 5-min (MoCA 5-min) ≥ 6	Diagnostic of psychiatric illness current or during last 5 years
Competency in Catalan or Spanish	Geriatric Depression Scale (GDS-15) > 9
Adequate visual, auditory, and fine motor skills	Consumption of psychopharmacological drugs current or during last 5 years; or more than 5 years throughout life
Acceptance of participation in the study and signature of the informed consent	History of drug abuse or alcoholism current or during last 5 years; or more than 5 years throughout life; >28 men and >18 woman unit of alcohol/week
	History of chemotherapy
	Contraindication to magnetic resonance imaging

*MMSE (Blesa et al., 2001); MoCA 5-min (Wong et al., 2015); GDS-15 (Martínez et al., 2002).*

### Assessments

Potential participants are screened by phone and an on-site personal interview; if eligible, informed written consent is obtained. Assessments are conducted in a clinical environment and organized into three appointments that take place at baseline – within 2 weeks prior to the start of the intervention, and again at 3 months within 2 weeks after the completion of the intervention (Table 2). (1) Medical assessment (30 min): review of medical history and current health status including cardiovascular risk factors and blood extraction between 8 and 9:30 AM following an overnight fast. (2) Cognitive assessment and physical status (2.5 h): administration of a battery of neuropsychological tests, psychological health, subjective performance, daily activities and PA questionnaires and a treadmill fitness test. In order to control the effects of acute exercise, participants are advised not to exercise prior to all appointments and cognitive tests are conducted before the CRF test. (3) Magnetic Resonance Imaging (MRI) scans (45 min): administration of a neuroimaging protocol to acquire structural and functional data of the brain. All assessments are carried out in two primary care centers except MRI scans that are performed in the Hospital Germans Trias i Pujol. All subjects receive an actimeter the first and last week of intervention to track their daily activity and determine if participants meet the intervention protocol. The same team of psychologists, which administers cognitive tests, and nurses, who collect general health data, follow the protocol in all the centers.

**TABLE 2 T2:** Assessments.

	**Enrollment and screening**		**Baseline assessments** **(within 2 weeks prior to the start of the intervention)**			**Intervention**			**Post-intervention assessments** **(within 2 weeks after the completion of the intervention)**		
				
	**Telephone screening**	**Visit 1: Screening**	**Visit 2: Baseline assessment**	**Visit 3: Baseline assessment**	**Visit 4: Baseline assessment**	**Visit 5: Initial intervention**	**Visit 6: Mid-intervention**	**Visit 7: Final intervention**	**Visit 8: Post-intervention assessment**	**Visit 9: Post-intervention assessment**	**Visit 10: Post-intervention assessment**
First review of criteria	X										
Montreal Cognitive Assessment 5-min (MoCA 5-min)	X										
Information of study	X	X									
Exhaustive review of criteria		X									
Informed consent form		X									
Mini-Mental State Examination (MMSE)		X								X	
Geriatric Depression Scale (GDS-15)		X								X	
Medical history			X								
General health status			X						X		
Blood extraction			X						X		
Battery of neuropsychological tests				X						X^1^	
Psychological health and daily activities scales				X						X	
Physical activity questionnaire (VREM)				X						X	
Cardiorespiratory fitness (Rockport 1-mile walk test)				X						X	
Magnetic resonance imaging					X						X
Information about intervention						X					
Follow-up adherence questions^2^							X	X			
Actimeter^3^ (Polar Loop^®^)						X		X			
Intervention follow-up diary^4^						X	X	X			

*^1^All of tests except vocabulary subtest; ^2^This information is also collected in phone calls every 2 weeks between visits; ^3^Participants carry the actimeter the first and last week of training; ^4^Participants record the diary every day during the intervention; MoCA 5-min (Wong et al., 2015); MMSE (Blesa et al., 2001); GDS-15 (Martínez et al., 2002); VREM – Reduced Minnesota leisure time physical activity questionnaire (Ruiz et al., 2012); Rockport 1-mile walk test (Kline et al., 1987).*

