### Randomization

Participants are randomly assigned to the groups stratified by sex, age, and education. The allocation sequence consists of a random list of these variables all combined and was generated by a statistician. The intervention staff is responsible for the allocation and informs participants at the first intervention visit. Assessors are blinded to the sequence and the group assignment of the participants. Blinding will only be broken for medical reasons.

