#### Aerobic Exercise (AE)

The training program is based on international guidelines of physical exercise (World Health Organization [WHO], 2010). Participants are instructed to walk briskly in one continuous bout (45 min for 5 days, 225 min per week); intensity and duration are initiated in a stepwise manner in order to reduce the possibility of injury. The first week they must walk 30 min at 9–10 on the BRPES (Borg, 1982) considered light intensity. Time is increased to 45 min with the same intensity during the second week. During the rest of the program (10 weeks), they maintain the 45 min and increase the intensity of the activity to a moderate-high effort that corresponds with 12–14 in the same scale. Subjects are trained to use the BRPES (Borg, 1982) and to record this intensity and frequency of activity in a diary.

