##### Physical activity

Information about energy expenditure of PA performed during the last month is obtained by the Reduced Minnesota leisure time PA questionnaire (Ruiz et al., 2012). Polar Loop^®^ actimeter (Polar Electro, NY, United States) registers daily PA (hours, steps, km, kcal) and sleeping (hours, %) parameters. Energy expenditure is the very first consequence of exercising. We aim to identify if baseline energy expenditure is related to baseline CRF and describe how the change in energy expenditure is related to physiological molecular correlates, CRF and to brain and cognitive outcomes.

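### The first actimeter recording is an on-treatment value for AE and COMB, so using it as a baseline biases the device-measured activity contrast towards no effect

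*Protocol article*

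**What the plan says.** - **When the device is worn.** Assessments: "All subjects receive an actimeter the first and last week of intervention to track their daily activity". The Table 2 footnote agrees: "Participants carry the actimeter the first and last week of training". Table 2 marks the actimeter at Visits 5 and 7 only, both under the intervention columns. Baseline Visits 2 to 4 carry no mark.
- **What participants know by then.** Under Randomization, the intervention staff "informs participants at the first intervention visit". That is Visit 5, where the device is first marked.
- **What AE and COMB do in week 1.** Aerobic Exercise (AE): "The first week they must walk 30 min at 9–10 on the BRPES". Week 2 has 45 min at the same intensity, and the remaining 10 weeks have 45 min at 12–14 on the scale. Combined Training (COMB) applies the same walking instructions.
- **What the device is for.** Assessments gives two purposes: tracking daily activity, and to "determine if participants meet the intervention protocol". Table 4 also lists its hours, steps, km and kcal as secondary outcomes.
- **What is to be shown.** Secondary hypothesis 2 in Aims of the Study expects AE and COMB to "increase CRF and energy expenditure in daily activity compared to cognitive and control conditions".
- **How it is analysed.** Statistical Analyses compares baseline values between groups to choose adjustment variables, compares time points within each group, decides whether to control for baseline, and tests condition by time. The secondary hypotheses follow the same pipeline, in the per-protocol sample.
- **The parallel measures.** The VREM questionnaire and the Rockport walk test are marked at Visit 3 (before the intervention) and Visit 9 (after it).

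**The concern.** A change score, a condition-by-time interaction or a baseline-adjusted comparison needs a first measurement that treatment has not touched. For the actimeter there is none: its first value is taken after allocation, while two of the four arms are already carrying out the behaviour that the device records.

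Each step of the pipeline is affected. The baseline comparison could flag a difference caused by treatment as a chance imbalance to be adjusted away. Controlling for that value removes part of the effect. The condition-by-time test subtracts the early part of the effect.

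The actimeter is the only device-based measure of daily activity in the trial. The alternative, VREM, is self-reported by people who know their group. An attenuated actimeter result could be read as showing that the walking programme did little to daily activity, when part of the effect had simply been subtracted.

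**Working it through.** **Inputs** (Aerobic Exercise section unless stated)
- Full schedule: 45 min on 5 days. The article states 225 min per week; 45 × 5 = 225, so the figure is reproduced.
- Week 1: 30 min per session. At the general 5-day frequency (Intervention section), 30 × 5 = 150 min/week. That five sessions are done in week 1 is an assumption.
- CCT and control: no walking prescribed in either recording week.
- Other daily activity is assumed equal in the two recording weeks, so that it cancels.

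**1. Prescribed minutes, change score or condition by time**
- Rise from an untreated start: 225 − 0 = 225 min/week.
- Rise that the two recordings can show: 225 − 150 = 75 min/week.
- Share retained: 75 / 225 = 33%; share subtracted: 150 / 225 = 67%.
- The comparison arms have no prescribed walking at either time, so the between-arm contrast loses the same 150 min/week. The direction is towards no effect.

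**2. Prescribed minutes, adjustment for week 1**
- Adjusted contrast = 225 − b × 150, where b is the within-arm slope of last-week on week-1 activity. The article gives no b.
- b = 1 gives 75, the same as the change score; b = 0 gives 225, no loss. Any positive slope attenuates the contrast.

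**3. Measures that depend on intensity (steps, km, kcal)**
- Intensity rises from 9–10 to 12–14 on the exertion scale, so a week-1 minute should yield less than a last-week minute. Let r be the ratio of week-1 to last-week yield per minute. The article does not give r, so it is an assumption.
- Share retained = 1 − 150 × r / 225.

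| r | share retained |
|---|---|
| 1.0 | 33% |
| 0.8 | 47% |
| 0.6 | 60% |
| 0.5 | 67% |

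**4. Sensitivity to falling adherence (minutes)**
- Full adherence in week 1 and 80% in the last week: 0.80 × 225 = 180, and 180 − 150 = 30 min/week, or 30 / 180 = 17% of the true rise.
- Recorded change reaches zero when last-week adherence is 150 / 225 = 67%, although those participants would still be walking 150 min/week more than before the trial.

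**5. Last-week values only**
- With no week-1 term in the model, the between-arm contrast at full adherence is 225 − 0 = 225 min/week. Nothing is subtracted.

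**The case against.** The strongest reply is that the article never names week 1 as the comparator for an efficacy change. Table 2 puts the actimeter among the intervention items, beside the diary and the adherence questions. Data Quality uses it to check diaries and phone calls for coherence, and for that purpose wear in the first and last weeks is sensible. The Intervention section does say that the device is received at baseline, but this describes when it is handed over with the instructions and does not define an outcome baseline. The pipeline paragraph does not mention the actimeter, and the article leaves detailed procedures to later papers.

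Much of this stands. The adherence role is legitimate and unharmed, and an unattenuated last-week comparison remains open to the analysts. It does not remove the point, because the actimeter parameters are also listed as outcomes, the only analysis described for secondary hypotheses relies on baseline and time, and the wear schedule is fixed. No later analysis plan can recover an unrecorded pre-treatment week.

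Two stronger readings are tempting and are not supported.
- **Most of the effect is lost on every actimeter measure.** The two-thirds loss is shown only for prescribed minutes. The rise in intensity after week 2 makes a smaller loss likely for steps, km and kcal.
- **The planned associations of activity change with fitness, brain and cognition are distorted, or hypothesis 2 cannot be tested.** The Physical activity section plans to "describe how the change in energy expenditure is related to physiological molecular correlates" and other outcomes, but the same section ties energy expenditure to VREM, which has an untreated baseline. Reading that plan as VREM change is at least as natural, and hypothesis 2 can be tested on VREM and fitness.

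**Conclusion.** The point holds in a limited form. The week-1 actimeter value is an on-treatment measurement for AE and COMB. If it serves as baseline or covariate, as the pipeline for secondary hypotheses implies, the contrast with CCT and control is biased towards no effect. The retained share is 33% for prescribed minutes, and about 33% to 67% for measures that depend on intensity over the assumed range of r.

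These sizes rest on five sessions in week 1, equal adherence in both recording weeks, stable background activity, and use of a change score or condition-by-time test. Covariate adjustment would lose less if the within-arm slope is below 1. Lower adherence in the last week than in the first would make the attenuation worse.

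The reach is narrow: one set of secondary outcomes. VREM, cardiorespiratory fitness and the primary cognitive outcomes are untouched. It still merits a correction, because the analysis choice changes the result and costs almost nothing to settle in advance.

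**What to change.** **In the analysis plan, for all participants:**
1. State that week-1 actimeter data are on-treatment and serve as an adherence check only. They are not used as a baseline, as a covariate, or in the baseline comparison that selects adjustment variables.
2. Analyse the actimeter outcomes as a between-arm comparison of last-week values, adjusted for baseline VREM and the planned covariates (sex, age, years of education).
3. Use VREM for change from baseline in activity and for the associations between activity change and other outcomes.

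This costs a few sentences and no new data. What is given up is a device-measured change within person.

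**For participants still to be enrolled, if any:** add an actimeter week inside the existing two-week baseline window, with the device handed out at Visit 3 or 4. This would give a true baseline. The cost is one extra wear week per participant. If the first week is moved instead of added, the device-based adherence check in week 1 is lost and only the diaries and phone calls cover that week. Recruitment started in November 2015, so this may come too late for many participants; the analysis change does not depend on it.
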